### Data management

Data collection, entry, management, and quality assurance are conducted at each enrollment site. However, all standard operating procedures for data collection and management are identical across the enrollment sites. We have developed standardized REDCap data collection forms and implemented procedures for quality control. Data collection forms provide clear instructions to guide data entry and contain pre-programmed skip patterns, real-time range checks, and internal logic to minimize missing data and facilitate cleaner data at capture. Study data will be entered directly (in real-time) into REDCap using password-protected laptop computers or tablets. Data entered in Uganda while offline will be uploaded to a secure University of California San Francisco server on a daily basis. All data will undergo weekly checks for completeness, consistency, accuracy, and range criteria. Queries performed on the database will be reviewed, verified, and corrected every 2 weeks.

### Statistical methods

#### Primary and secondary outcomes

The primary trial outcome is a 2-year composite endpoint of microbiologically confirmed incident TB and all-cause mortality, measured as time to first diagnosis of incident TB or death from any cause. The primary analysis will be by intention-to-treat (ITT), including all participants randomized without regard to the results of baseline TB screening, and we will use a two-sided alpha (0.05 significance) in assessing the effect of the intervention on the primary outcome. Participants with prevalent TB will be included in the analysis to preserve the randomized groups (the ITT principle) but excluded from the outcome of incident TB because subsequent disease is more likely to represent relapse or failure (and these participants will not routinely receive TPT). Time from randomization to first event (diagnosis of incident TB or death from any cause) will be analyzed using the log rank test and Cox proportional hazards models, adjusted for the study site. If data are missing or a patient is lost to follow-up, a patient’s data will be censored in the analysis at the date of last known contact. We will also use the Mantel-Haenszel method to determine standardized incidence rates and incidence rate differences. Balance at baseline on all known and suspected prognostic factors will be assessed, and if important imbalances are found (e.g., differences in median baseline CD4 count), a sensitivity analysis will be conducted using a Cox model to adjust for these factors. We will also assess the impact of clinician-initiated co-interventions (e.g., clinician-initiated TPT, clinician-initiated TB treatment) on the primary outcome. We will conduct a sensitivity analysis in which these participants are censored as soon as they are initiated on TPT or TB treatment by non-study clinicians. Standard checks for variation by enrollment site will also be planned. Secondary outcomes for the primary objective include the individual primary endpoints (TB incidence and mortality analyzed separately) and 2-year isoniazid-resistant TB incidence and will be analyzed using a similar approach; there will be no adjustment for multiplicity since these are pre-specified secondary outcomes.

To evaluate intermediate outcomes on the pathway to the composite primary trial outcome, we will determine the proportion of randomized participants initiating TPT (prescribed TPT), the proportion of randomized participants completing TPT (≥90% TPT pills taken), the proportion of randomized participants diagnosed with prevalent TB, and the proportion of randomized participants with prevalent TB completing TB treatment (by clinic record review). The primary analysis will be by ITT, with the outcome of initiating any TPT based on actual events, irrespective of whether the algorithm was followed. Participants eligible for 3HP based on the results of baseline screening (i.e., study-initiated TPT) may decline to initiate 3HP after randomization despite being prescribed 3HP; these participants will be counted as not having started TPT. Participants who were initiated on TPT during study follow-up (i.e., clinician-initiated TPT for participants who were classified as ineligible for 3HP based on the results of baseline screening) will be counted as having started TPT; 6 months of daily isoniazid (IPT) is currently the most common TPT regimen available for routine clinical use. We will compare the proportion of PLHIV initiating any TPT (study- and clinician-initiated TPT) and the proportion of PLHIV completing TPT (the denominator will be the total number of participants in the study arm), calculating the risk difference and 95% confidence intervals (CI) using standard methods, adjusted for study site using Cochran-Mantel-Haenzsel weights. If respective data on an outcome is missing or a patient is lost to follow-up, it will be assumed that the patient did not initiate nor complete TPT (depending on what data are available). Our working hypothesis is that POC CRP-based TB screening will increase the proportion of PLHIV initiating and completing TPT by at least 40%, relative to symptom-based screening. We will compare the proportion of PLHIV with screen-positive prevalent TB and the proportion of PLHIV with screen-positive prevalent TB completing TB treatment, calculating the risk difference and 95% CIs using standard methods, adjusted for study site using Cochran-Mantel-Haenszel weights. Our working hypothesis is that the proportion of PLHIV with screen-positive prevalent TB will be similar in each arm, and we expect the upper bound of the CI of the difference will be no more than 5%. We consider this margin of 5% sufficiently small to conclude equivalence.

We will repeat the primary analysis in the following pre-specified sub-groups: by age, gender, enrollment site, and CD4 strata (< 50, 50–199, ≥200 cells/μL). Safety data related to missed diagnoses of prevalent TB, acquired drug-resistant TB, and TPT-related serious adverse events will be tabulated by study arm.

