### Participant timeline

After baseline study procedures, routine clinic staff will provide all further care and follow-up for HIV, TPT, and/or active TB treatment. Routine clinical care for all patients initiated on ART includes blood draw for pre-ART labs, HIV viral load at 6 months and as appropriate thereafter, and clinic visits at weeks 2 and 6 and then months 3, 6, 12, 18, and 24 post-ART initiation. Patients initiated on 3HP or TB treatment have additional visits for active TB screening, medication adverse event (AE) monitoring, adherence assessments, and refills, per routine clinic protocols. To capture clinical and outcome data for this trial, we will conduct brief follow-up interviews and extract relevant data from the clinic medical record at regular intervals for 2 years (months 3, 6, 12, 18, and 24). At the final (24-month) study visit, we will collect sputum specimens from all participants who have not been treated for TB during the study for the final active TB assessment. Table 1 describes the schedule of study activities performed by study staff and the schedule of clinic activities performed by routine clinic staff for PLHIV initiating ART.

**Table 1 Tab1:** Schedule of study activities

Timepoint	Entry	Weeks				Months						
	0	2	4	6	8	3	4	5	6	12	18	24

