### Outcomes

The primary trial endpoint is a composite outcome of microbiologically confirmed incident TB and all-cause mortality, measured as time to first diagnosis of incident TB or death from any cause. Microbiologically confirmed incident TB is defined as active TB diagnosed by either culture, one non-trace positive Xpert Ultra result or two trace-positive Xpert Ultra results, or positive urine LAM result from 3 months after randomization to the end of follow-up (at 2 years, or at the time of last contact for participants who are lost to follow-up). To assess active TB status at the end of follow-up, 2 spot sputum specimens will be collected from all participants who have not taken anti-TB treatment during the study at the final (24 months) study visit for sputum Xpert Ultra testing, liquid culture, and drug susceptibility testing (for participants who received any TPT). Secondary outcomes are presented in Table 2.

**Table 2 Tab2:** Secondary outcomes of the TB SCRIPT trial

Outcome	Numerator	Denominator

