#### Final TB status assessment

For all participants who have not taken anti-TB treatment during follow-up, we will collect 2 spot sputum specimens at the final (24 months) study visit for sputum Xpert Ultra testing; repeat Xpert Ultra testing, if the initial test is trace-positive; and liquid culture and drug susceptibility testing (DST). Speciation testing will be performed on all positive cultures to confirm the presence of *M. tuberculosis* complex using Ziehl-Neelsen smear microscopy for detection of acid-fast bacilli and SD MPT64 (Standard Diagnostics Bioline TB Ag MPT64, South Korea) for rapid *M. tuberculosis* antigen detection. DST will include susceptibility testing to all first-line TB medications including isoniazid and rifamycin-based drugs. Participants will be classified as having incident TB if at least one of the following criteria are met: at least one sputum culture positive for *M. tuberculosis* complex, one non-trace-positive Xpert Ultra result, or two trace-positive Xpert Ultra results.

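### Censoring at last contact gives month-24 attenders with no usable sputum result the same event-free follow-up as those who tested negative

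*Protocol article*

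**What the plan says.** All references are to the protocol article.

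- **Endpoint and model** (Statistical methods, Primary and secondary outcomes). The composite is "measured as time to first diagnosis of incident TB or death from any cause", and time to first event "will be analyzed using the log rank test and Cox proportional hazards models, adjusted for the study site".
- **Censoring rule** (same section). One rule serves two situations: "If data are missing or a patient is lost to follow-up", the patient's data "will be censored in the analysis at the date of last known contact". Missing data is named separately from loss to follow-up. The sensitivity analyses described there concern baseline imbalance and TPT or TB treatment started by non-study clinicians.
- **Final assessment** (Outcomes). At month 24, "2 spot sputum specimens will be collected from all participants who have not taken anti-TB treatment during the study". Follow-up ends at 2 years, and at last contact only for those lost.
- **What counts as TB at that visit** (Final TB status assessment): "at least one sputum culture positive for *M. tuberculosis* complex, one non-trace-positive Xpert Ultra result, or two trace-positive Xpert Ultra results".
- **TB detection before month 24** (Participant timeline). Routine staff provide care, and the study team states that "we will conduct brief follow-up interviews and extract relevant data from the clinic medical record at regular intervals for 2 years".
- **Table 2, section A.** The denominator of 2-year TB incidence is everyone randomized to the arm minus those treated for prevalent TB.

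**The concern.** Attendance at month 24 shows that a participant is alive. It does not show that TB was looked for. Last contact is therefore a sound censoring date for death, but not for TB that only the month-24 sputum could reveal. An attender who cannot produce sputum, declines, or has an invalid or contaminated specimen gets the same record as one whose specimens were negative: full person-time and no event. Table 2 has the same feature, because such a person stays in the denominator and cannot add a month-24 event to the numerator.

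Some missing specimens are foreseeable. At baseline, sputum is taken from screen-positive participants and induced if needed. At month 24 it is asked of everyone not treated for TB, many of them well. The 12% allowance in the sample size covers loss to follow-up, not attenders without a result.

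At stake are the absolute TB and composite risks, a little power, and the arm comparison if the untested share differs between arms.

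**Working it through.** **Inputs from the Sample size section.** Control 2-year mortality 5.2%, TB 7.3%, composite 12.5%; 35% relative reduction; 860 per arm; 12% loss; two-sided alpha 0.05.

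**The plan's own figure.** 860 × 0.88 = 756.8 evaluable per arm. Expected events are 756.8 × 0.125 = 94.6 and 756.8 × 0.08125 = 61.5 (stated: 95 and 62). A two-proportion comparison at 757 per arm gives power 0.80, as stated. The sample size is sound and is not in question.

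**Assumed inputs (not in the documents).** f = share of incident TB found only by month-24 sputum, taken as 25–75%. m = share of those due sputum who attend without a usable result, taken as 10–30%.

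**Step 1: absolute risk under the rule.** If the untested carry the same TB risk as the tested, observed composite = 5.2% + 7.3% × (1 − f × m).

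| f | m | Observed TB | Observed composite | Power, equal m, true ratio 0.65 |
|---|---|---|---|---|
| – | 0 | 7.30% | 12.5% | 80% |
| 25% | 10% | 7.12% | 12.3% | 79% |
| 50% | 20% | 6.57% | 11.8% | 77% |
| 75% | 30% | 5.66% | 10.9% | 74% |

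TB risk is understated by f × m, that is by 2.5%, 10% and 22.5% in relative terms. Missed TB events over both arms are 757 × f × m × (0.073 + 0.65 × 0.073): about 2 at the low end and 21 at the high end.

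**Step 2: taking the untested out of the month-24 risk set.** Use f = 50%, m = 20% and 757 per arm. Deaths plus earlier TB number 757 × (0.052 + 0.0365) = 67, leaving 690 at risk at month 24. Sputum finds 757 × 0.0365 × 0.8 = 22.1 cases.

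- Untested kept in the risk set: (67 + 22.1)/757 = 11.8%.
- Untested taken out: the month-24 hazard is 22.1/(690 × 0.8) = 0.040, and 1 − (690/757) × 0.960 = 12.5%.

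The true value is recovered, provided sputum is missing at random.

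**Step 3: ratio between arms.** With equal m, the factor (1 − f × m) applies to TB in both arms and the composite ratio stays at its true value of 1.00 or 0.65. With unequal m, f = 50% and no true effect:

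- Control 10%, CRP 20% untested: (5.2 + 7.3 × 0.90)/(5.2 + 7.3 × 0.95) = 11.77/12.135 = 0.97. For TB alone, 0.90/0.95 = 0.947.
- Control 20%, CRP 10% untested: 12.135/11.77 = 1.03.
- First case, with the untested at half the month-24 TB risk: (12.5 − 3.65 × 0.20 × 0.5)/(12.5 − 3.65 × 0.10 × 0.5) = 12.135/12.3175 = 0.985.

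Over f = 25–75%, the first case runs from 0.985 to 0.954 and the second from 1.015 to 1.048. If the true ratio is 0.65 and f = 50%, the two cases read 0.63 and 0.67.

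**Step 4: is a 10-point gap plausible through TPT?** The plan expects 55% versus 15% to start 3HP. If TPT takers are untested δ more often, the gap between arms is 0.40 × δ. A 10-point gap needs δ = 25 points (about 31% versus 6% untested). With δ = 10 points the gap is 4 points. At 10% versus 14% untested and f = 50%, the ratio is (5.2 + 7.3 × 0.93)/12.135 = 0.99.

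**The case against.** The best counter-argument is that this is detail for the full protocol or analysis plan, neither of which is shown. The censoring sentence is generic and does not mention sputum. That is fair as far as it goes, and an unseen plan may already refine the rule. But the article does state a rule, the rule names missing data, and applied as printed it has this result. An analysis plan that follows it would inherit the problem.

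Several stronger readings are tempting and are not supported:

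- *These people were never tested for TB.* Routine clinicians may order TB tests at any time (Blinding), and records are reviewed throughout. The accurate statement is that they were not tested at month 24.
- *The plan declares the untested TB-free.* It does not. They are formally censored. At the end of follow-up, however, that produces the same record as a negative test.
- *The CRP arm gains a spurious advantage.* No direction can be inferred. More missing sputum in the control arm would bias against CRP. 3HP is 12 weekly doses started early in the trial, and participants are blinded, so a large TPT effect on sputum at 2 years is doubtful. A 20-point gap between arms would need TPT takers to be untested 50 points more often.
- *Well people give less sputum, so the full bias applies.* If the untested are well they probably have less TB, and the bias shrinks. Earlier censoring could then overstate TB somewhat, because it assigns them the risk of those tested.

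It is also true that the article does not say whether a month-24 event is dated at the visit or when the culture result arrives. Either way, the untested and the test-negative have identical records.

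**Conclusion.** The point holds as a minor one. As printed, the rule gives participants due month-24 sputum who attend without a usable result the same full event-free follow-up as those who tested negative. If the untested have no more TB than the tested, TB risk is understated by up to f × m, a relative 2.5–22.5% over the assumed ranges. With equal missingness the ratio between arms is unbiased, and the cost is understated absolute risk and power of 74–79% instead of 80%. With unequal missingness the bias can run either way and is probably small: about 0.97 or 1.03 under no true effect for a 10-point gap at f = 50%, and nearer 1 if the untested have less TB.

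All effect sizes rest on assumed shares. The point concerns attenders, not those lost to follow-up, and it should not be read as a fault in the sample size or as evidence that the trial favours CRP.

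**What to change.** 1. Add one sentence to the censoring rule. For participants who are due month-24 sputum (no anti-TB treatment during the study) and have no valid result, censor the composite and the TB endpoint just before the month-24 visit, as the last TB-evaluable date. Deaths stay fully counted in the mortality analysis. The limit matters: participants already treated for TB are not sampled by design, and their follow-up should not be cut.
2. Report by arm the share of those due month-24 sputum who have a valid result.
3. Add one sensitivity analysis that imputes the missing month-24 result from arm, TPT, CD4 and site, because earlier censoring assumes that sputum is missing at random.
4. Carry the same handling into Table 2. A new censoring sentence alone leaves its fixed-denominator 2-year TB incidence unchanged, so add a Kaplan-Meier estimate or an evaluable denominator as a sensitivity analysis.

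The cost is a few days of follow-up for the untested and one added analysis. No visit, procedure or sample size changes.

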### Objectives

The primary objective of TB SCRIPT is to compare the impact of POC CRP-based with symptom-based TB screening on 2-year TB disease outcomes. We will randomize participants to either POC CRP-based (intervention) or standard-of-practice symptom-based TB screening (control). All participants who screen positive will undergo confirmatory TB testing, while only participants who screen negative will initiate 12 weekly doses of isoniazid and rifapentine (3HP), a short-course TPT regimen. We will follow all eligible participants for 2 years to assess TB incidence and all-cause mortality. At the final study visit, we will collect sputum to ascertain active TB status from participants who have not been diagnosed with or treated for active TB during follow-up. The primary hypothesis for this objective is that participants randomized to POC CRP-based TB screening will have lower combined 2-year TB incidence and mortality (composite primary trial outcome), relative to participants randomized to symptom-based screening. The second objective is to compare the impact of POC CRP-based with symptom-based TB screening on (1) TPT uptake and (2) prevalent TB case detection, intermediate outcomes on the pathway to the combined primary trial outcome. The primary hypothesis for this objective is that participants randomized to POC CRP-based TB screening will have higher rates of TPT uptake and completion, determined via objective monitoring, and similar rates of prevalent TB case detection relative to participants randomized to symptom-based screening.

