### Trial design and study setting

The TB SCRIPT trial is a phase 3, single-blinded, multi-center, randomized superiority trial evaluating the clinical impact of POC CRP-based TB screening on immediate and longer-term outcomes of PLHIV in Uganda. Uganda is among the world’s 30 high HIV/TB burden countries with an HIV prevalence of 6.2% and an annual TB incidence of 253 cases per 100,000 [1, 24]; among all TB cases, HIV prevalence is estimated at 45% [25]. Data from the 2014–2015 national TB prevalence survey estimate that half of all TB cases go undiagnosed each year, and the overall TB burden is greatest in urban areas [24].

We will randomize 1720 PLHIV presenting for routine ART initiation in three clinics (two public and one non-government/non-profit) in Kampala, Uganda, to either POC CRP-based TB screening (intervention) or symptom-based TB screening (control) with a 1:1 allocation ratio over a 2-year period. After randomization, we will perform baseline TB screening in accordance with the participant’s assigned TB screening strategy. Based on the results of baseline TB screening, we will either collect clinical specimens (urine, sputum) for confirmatory TB testing (urine lipoarabinomannan [LAM], sputum Xpert Ultra MTB/RIF, if screen-positive) or assess 3HP eligibility (if screen-negative, Fig. 1). Supported by study staff, clinic staff will provide all further care and follow-up for HIV, 3HP, and/or active TB, per routine clinic protocols. We will subsequently extract relevant clinical and outcome data from the clinic medical record at regular intervals (months 3, 6, 12, 18, and 24) for 2 years and collect sputum specimens for comprehensive TB testing (sputum Xpert Ultra, culture and drug susceptibility testing [DST]) at the final (24 months) study visit to ascertain 2-year active TB status.

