### Sample size

The sample size calculations are primarily based on the primary objective (which requires a larger sample size). We expect 2-year mortality of 5.2% and 2-year TB incidence of 7.3% in the control arm [4, 28]. Assuming a two-sided alpha of 0.05 and 12% lost to follow-up, a sample size of 860 participants per arm (1720 total) will provide 80% power to detect a relative reduction of 35% in the 2-year combined outcome (from 12.5% [*n* = 95] to 8.1% [*n* = 62]). This sample size will also provide 85% and 90% power if 2-year mortality is 6.8% and 8.8%, respectively (Table 3). This sample size also gives 80% power to detect a smaller 29% relative reduction if the 2-year combined TB incidence and mortality in the control arm is as high as 17.5% with a 10% loss to follow-up. We will analyze the primary outcome as time-to-event and therefore expect this study power assuming binary outcomes will be a lower bound for study power.

**Table 3 Tab3:** Power calculations (power to detect 35% difference in the combined 2-year TB incidence and mortality outcome when 2-year TB incidence is 7.3%)

2-year mortality		Power
POC CRP-based screening	Symptom-based screening	
3.4%	5.2%	0.80
4.4%	6.8%	0.85
5.1%	7.9%	0.88
5.7%	8.8%	0.90

For the secondary objective, based on published estimates of specificity from similar settings, we estimate no more than 15% of all patients in the control arm will initiate 3HP (and 13.5%, or 90% of all control patients initiating 3HP, will complete 3HP) [16, 17, 20]. This sample size will give more than 90% power to show improvements in the proportion of all patients initiating 3HP by an absolute difference of 6% of more, which is much less than what is considered clinically important; we anticipate 55% of all patients in the POC CRP will initiate 3HP (and 55% of all patients will complete 3HP).

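### The primary Cox model adjusts for site only; baseline CD4 is adjusted for only if an undefined imbalance appears, which forgoes a small power gain and makes the adjusted analysis depend on observed balance

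*Protocol article*

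**What the plan says.** In the Protocol article, under Statistical methods (Primary and secondary outcomes), time to the composite of incident TB or death "will be analyzed using the log rank test and Cox proportional hazards models, adjusted for the study site". No other covariate is named for the primary analysis. The same section then has baseline balance inspected across an open set of known or suspected prognostic factors. The rule it states is: "if important imbalances are found (e.g., differences in median baseline CD4 count), a sensitivity analysis will be conducted using a Cox model". That model would carry the imbalanced factors as covariates.

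Elsewhere in the article:
- **Eligibility criteria** require a CD4 count of 350 cells/μL or lower, and Table 1 schedules CD4 at entry.
- **Random allocation** is stratified by site only.
- **CD4 categories** (<50, 50–199, ≥200 cells/μL) are already fixed, but only for subgroups: "We will repeat the primary analysis in the following pre-specified sub-groups".
- **Sample size** claims "80% power to detect a relative reduction of 35% in the 2-year combined outcome", calculated on two unadjusted proportions.

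**The concern.** CD4 is a baseline value the trial must obtain before enrolment, and the plan treats it as prognostic twice, as its example of an imbalance and as a subgroup factor. Leaving it out of the primary model gives away whatever precision it carries, in a design with no power in reserve at its base case.

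The conditional rule is the second problem. The plan states no cut-off for an important imbalance and no fixed covariate list, so the observed data settle both whether an adjusted result exists and what it contains. A chance imbalance just below whatever line is drawn would move the unadjusted estimate with no adjusted result beside it.

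**Working it through.** **1. The plan's power figure.** From Sample size: 860 per arm, 12% loss, control risk 12.5%, 35% relative reduction, two-sided alpha 0.05.
- Evaluable per arm: 860 × 0.88 = 756.8. CRP-arm risk: 12.5% × 0.65 = 8.125%. Mean risk: 0.103125.
- z = [0.04375 × √756.8 − 1.96 × √(2 × 0.103125 × 0.896875)] / √(0.125 × 0.875 + 0.08125 × 0.91875) = (1.2036 − 0.8430) / 0.4290 = 0.84, so power is **80.0%**. With the rounded 8.1% it is 80.5%.
- Time-to-event cross-check: HR = ln(1 − 0.08125) / ln(1 − 0.125) = 0.635. With 95 + 62 = 157 events, z = √(157/4) × |ln 0.635| − 1.96 = 0.89, so power is 81.3%.

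The stated 80% reproduces without any covariate.

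**2. What CD4 adjustment would add.** The article gives no CD4 effect or distribution, so both are assumptions. Trials of 1512 evaluable participants were simulated with exponential times and censoring at 2 years. Each scenario was calibrated so that the overall risks stay at 12.5% and 8.125%. A Cox model with arm only was compared with one adding the plan's three CD4 strata. Site was not simulated. There were 8000 replicates per row, and 1500 for the no-effect row.

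| Assumed HR (<50 / 50–199 / ≥200) | Assumed shares (%) | Power without CD4 | Power with CD4 | Gain (points) |
|---|---|---|---|---|
| 1 / 1 / 1 | 20/40/40 | 78.9% | 78.7% | none |
| 2 / 1.4 / 1 | 20/40/40 | 79.0% | 79.6% | 0.6 |
| 4 / 2 / 1 | 20/40/40 | 80.0% | 81.2% | 1.2 |
| 4 / 2 / 1 | 10/40/50 | 81.5% | 82.5% | 1.0 |
| 4 / 2 / 1 | 30/40/30 | 80.4% | 81.5% | 1.1 |
| 10 / 3 / 1 | 20/40/40 | 80.7% | 83.9% | 3.2 |

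The simulation error of each gain is about 0.2 to 0.3 points. The gain comes from a hazard ratio further from 1, not from a smaller standard error. In the 4/2/1 row (shares 20/40/40) the HR goes from 0.632 to 0.628 while the standard error of the log HR stays put (0.1648 and 0.1650). The gain is small because only about 157 / 1513.6 = 10% of participants have an event.

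In sample-size terms, from an 80% base, a 1-point gain is worth [(1.96 + 0.878) / (1.96 + 0.842)]² − 1 = 2.6% more participants. A 3-point gain is worth about 8%.

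**3. How the trigger behaves.** The standard error of a standardized CD4 difference is √(2/860) = 0.048. If an important imbalance meant an absolute standardized difference above an assumed cut-off, chance alone would trigger adjustment in:
- 30% of trials at 0.05,
- 3.8% at 0.1,
- under 0.01% at 0.2.

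Whether an adjusted result appears therefore depends almost entirely on where the line is drawn.

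**4. An imbalance the trigger could miss.** A two-standard-error difference is 2 × 0.048 = 0.096, just under a 0.1 cut-off. If the CD4-related log-hazard has an assumed SD of 0.5 to 0.9, the unadjusted log HR moves by about 0.096 × 0.5 = 0.05 to 0.096 × 0.9 = 0.09. Against a standard error of 2/√157 = 0.16, that is 0.3 to 0.5 in z. In the unfavourable direction, a true HR of 0.635 would read as about 0.67 to 0.69; a favourable imbalance would flatter it by as much.

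**The case against.** **The primary analysis is sound as it stands.** It is fixed in advance and adjusts for the one randomization stratum. Chance CD4 imbalance neither biases it nor inflates its type I error. This stands in full. A reader might infer that the primary model is chosen after seeing the data; the article does not support that, because only the supportive sensitivity model depends on observed balance.

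**No planned power is lost.** This also stands. The sample size assumed no adjustment and reproduces. A reader who simulates with 0.635 held as the CD4-conditional HR would see unadjusted power of 0.80, 0.76, 0.77 and 0.74 at log-hazard SDs of 0.5, 0.7, 0.9 and 1.1, and might infer that the site-only test falls well short of 80%. That set-up raises the CRP-arm risk above the planned value (to 8.45% at SD 1.1). Recalibrated to the plan's overall risks, unadjusted power is 0.81, 0.79, 0.80 and 0.81.

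**Large gains need extreme assumptions.** The same simulations, with a continuous predictor known without error, show gaps of about 1, 4, 4 and 7 points. A 7-point gain is tempting to quote, but SD 1.1 implies a hazard ratio of exp(2 × 1.96 × 1.1), about 75-fold, between the 2.5th and 97.5th percentiles, in a cohort already capped at CD4 350. Nothing in the article supports that.

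**Thresholds and covariate lists belong in the statistical analysis plan.** This holds only in part. A missing cut-off alone would be no finding. The article, however, states the rule that adjustment is conditional on observed imbalance. A cut-off supplied elsewhere would make the rule reproducible but still conditional.

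**The estimand shifts.** True, and a trial of screening policy may prefer the site-adjusted effect. The shift is small in the plausible range.

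**Conclusion.** The point holds as an inexpensive improvement, not as a defect that invalidates the primary result. The textual facts are firm: site-only primary model, CD4 available for essentially everyone, and adjustment only on an undefined trigger and only as a sensitivity analysis.

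The forgone gain is about 0.6 to 3 power points if CD4 is prognostic at the assumed hazard ratios, about 1 point for a fourfold contrast between extreme strata, and essentially none if it is not. The direction is secure whenever CD4 is prognostic. The size rests on CD4 effects and stratum shares that the article does not give.

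The case against the trigger does not rest on power. It makes the existence and content of the adjusted analysis depend on observed balance, and may leave a moderate imbalance without an adjusted result.

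**What to change.** - **Preferred:** name the Cox model with site and baseline CD4 (continuous, or the three categories already fixed for subgroups) as the primary analysis, and state that the primary p-value comes from it. Report the site-only log-rank test and Cox model as supportive.
- **Minimum:** keep the site-only model as primary, but specify one CD4- and site-adjusted Cox model that is always run. This removes the dependence on observed balance but not the forgone power.
- **Either way:** delete the imbalance trigger. Baseline balance can still be described.

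The change is a sentence or two, made before outcomes are examined by arm. Trial status reports recruitment as still ongoing. It needs no new data or participants, and the sample size stands. If CD4 proves not to be prognostic, nothing material is lost. The one cost is that the primary hazard ratio becomes conditional on CD4, which the plan should say.
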